### 3.3. Data Collection and Statistical Analysis

All data will be entered into a predesigned, password protected electronic database by two independent researchers who will be blinded to the allocation groups. All statistical analyses of the data will be performed using the SPSS program V.21.0. A *p* value < 0.05 will be considered statistically significant. For cases in which we do not finish all the treatment, we selected intention-to-treat (ITT) analysis to avoid the effects of crossover and drop-out. Measured data will be expressed as mean ± SD (x ±s) if it obeys a normal distribution or approximate normal distribution. The median (interquartile range [IQR]) will be used if the data do not obey the normal distribution and count data will be expressed in terms of the number of cases. We will use chi-square tests for categorical data and two sample *t*-tests or Wilcoxon rank sum tests for continuous data, according to whether the data are normally distributed or not. The variance analysis will be performed for the difference between groups and within the group. The stratified analysis will be performed to control the confounding factor if necessary.

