## 3. Results

The target of this study focuses on four types of parameters divided into primary, secondary, and exploratory outcomes. Primary outcomes refer to hormonal parameters, and secondary to anthropometric and metabolic parameters. Exploratory outcomes are related to quality-of-life analysis and will be performed using the Medical Outcomes Study 36-Item Short Form Health Survey [50], the Zung Self-Rating Anxiety Scale [51], and the Zung Self-Rating Depression Scale [52] (Table 3). All the questionnaires used are validated for Portuguese language. Outcome measures will be collected at baseline, 6 weeks, 12 weeks, and 6 months after the last acupuncture treatment (Table 2).

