### 4.2. Proposed Trial

To overcome the described limitations found in the literature on PCOS women studies, we propose an RCT with a sample of 120 women. This large sample would be important to increase the probability of including participants from all 4 phenotypes of latest Rotterdam criteria. Additionally, we will include a control group. Not all the previous studies presented blank controls [54,56] which, in our opinion, will be fundamental to understanding the effect of acupuncture on the PCOS condition. The design of our study follows the SPIRIT checklist and the international guidelines recommended for every released RCT [57]. Our study design will use the traditional Chinese medicine diagnostic with the respective rationale for the general condition of PCOS and the specific symptoms or signs. Thus, patients will be divided into two main phenotypes according to the TCM pathomechanism proposed by Lyttleton (2013). Although reproductive cycle normalization is a common indicator of a healthy reproductive status, we think it is more accurate to use the increase of the ovulation rate, balance of sex hormones, and improvement of the metabolic profile as the main indicators of the efficiency of the trial. For this reason, we suggest a study where the analysis of the results is divided in three parts: primary, secondary, and exploratory outcomes.

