**Figure 2 healthcare-10-01999-f002:**
[figure not shown]
Flowchart of the study period.

**Table 1 healthcare-10-01999-t001:** Rotterdam phenotypes for PCOS women with correspondent TCM phenotype.

Phenotype	Description
Rotterdam Phenotype A (classical PCOS) [46]	Hyperandrogenism + polycystic ovary morphology + ovulatory dysfunction—28.7%
TCM phenotype [47]	Spleen deficiency and phlegm stasis SP’s—32.27%
Rotterdam Phenotype B [46]	Hyperandrogenism + Ovulatory disfunction—19.0%
TCM phenotype [47]	Phlegm stasis and blood stasis—16.55%
Rotterdam Phenotype C [46]	Ovulatory disfunction + polycystic ovary morphology—37.3%
TCM phenotype [47]	Kidney deficiency and liver stasis—40.29%
Rotterdam Phenotype D [46]	Hyperandrogenism + polycystic ovary morphology—15.0%
TCM phenotype [47]	Kidney deficiency and blood stasis—10.89%

**Table 2 healthcare-10-01999-t002:** SPIRIT schedule of enrolment, interventions, and assessments.

	STUDY PERIOD														
	Enrolment	Allocation	Post-Allocation												Close-Out
TIMEPOINT	*−1 month*	0	* _W1_ *	* _W2_ *	* _W3_ *	* _W4_ *	* _W5_ *	* _W6_ *	* _W7_ *	* _W8_ *	* _W9_ *	* _W10_ *	* _W11_ *	* _W12_ *	*After 6 months*
ENROLMENT:															
Eligibility screen	X														
Informed consent	X														
Baseline assessments	X														
Allocation		X													
INTERVENTIONS:															
Active acupuncture															
		X	X	X	X		X		X		X		X	
Sham acupuncture															
		X	X	X	X		X		X		X		X	
ASSESSMENTS:															
*Diagnostic examination*	X														
*Primary and secondary outcomes*		X						X						X	X
*Life quality related questionnaires*	X	X						X						X	X

**Table 3 healthcare-10-01999-t003:** Primary, secondary, and exploratory outcomes that will be used in the study.

Primary	Secondary	Exploratory
**Hormonal Parameters**: Modified Ferriman-Gallwey score Ludwig visual score LH, mean (SD), mIU/mL FSH, mean (SD), mIU/mL LH/FSH Total free testosterone Androstenedione Progesterone, median (IQR), ng/mL Estradiol, median (IQR), pg/mL Sex hormone–binding globulin (SHBG), mean (SD), μg/mL Ovulation rate (%)	**Anthropometric parameters** Age (years) Height (cm) Weight (Kg) BMI (kg/m^2^) Waist circumference (cm) Waist Hip Ratio	**Quality-of-life scores**: Medical Outcomes Study 36-Item Short Form Health Survey Zung Self-Rating Anxiety Scale Zung Self-Rating Depression

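### Eleven primary outcomes share one unadjusted 0.05 threshold, with no lead outcome or primary time point, so the plan does not control the error rate of an efficacy claim

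*Protocol article*

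**What the plan says.** Section 3 of the protocol article assigns the tiers by type of variable: "Primary outcomes refer to hormonal parameters, and secondary to anthropometric and metabolic parameters". Table 3 then lists the primary column in full: "Modified Ferriman-Gallwey score Ludwig visual score LH, mean (SD), mIU/mL FSH, mean (SD), mIU/mL LH/FSH Total free testosterone Androstenedione", followed by "Progesterone, median (IQR), ng/mL Estradiol, median (IQR), pg/mL Sex hormone–binding globulin (SHBG), mean (SD), μg/mL Ovulation rate". That makes eleven variables.

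On timing, section 3 says: "Outcome measures will be collected at baseline, 6 weeks, 12 weeks, and 6 months after the last acupuncture treatment". Table 2 has the same three post-baseline assessments, and neither place marks one as primary.

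Section 3.3 gives one threshold, under which a p "value < 0.05 will be considered statistically significant". On methods it says "We will use chi-square tests for categorical data and two sample" t-tests or rank sum tests for continuous data, and adds analysis of variance between and within groups. It gives no order of testing, no adjustment, and no rule for how many of the eleven must be positive.

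Section 4.2 describes the main indicators of the trial differently: "we think it is more accurate to use the increase of the ovulation rate, balance of sex hormones, and improvement of the metabolic profile".

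**The concern.** When a whole class of variables is primary and each can be judged at 0.05, the study has several routes to a positive result, and the 5% level applies to each route separately. A reader of the final report could not tell whether one significant hormone out of eleven is an effect or what chance would be expected to produce.

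This matters because section 4.3 expects the trial to validate the acupuncture protocol for efficacy and safety, and section 5 presents the expected results as evidence of high methodological quality. Section 4.2 adds to the uncertainty: it sets the metabolic profile beside ovulation rate and sex hormones as a main indicator, while section 3 and Table 3 make it secondary.

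**Working it through.** **The plan's own figures.** The article states no family-wise error rate, so there is none to reproduce. Section 2.2 gives 60 women per TCM group with 20% withdrawal. Only the withdrawal step can be rebuilt: 48 / (1 − 0.20) = 60. The 48 is not derived, and no effect size, standard deviation, power or endpoint is given. The sample size therefore does not reveal a lead outcome either.

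**Inputs.**
- Primary outcomes: 11 (Table 3).
- Post-baseline times: 3 (section 3, Table 2).
- Threshold per test: 0.05 (section 3.3). Two-sided testing is assumed, because the article does not say; the independence results are the same either way.
- Correlations: not in the article, so a range is assumed.
- Reading rule: any one significant primary outcome counts as efficacy. This too is an assumption, because the article states no rule.

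**Independent tests.** P(at least one false positive) = 1 − (1 − 0.05)^k.
- One time, k = 11: 1 − 0.95^11 = 0.431.
- Three times, k = 33: 1 − 0.95^33 = 0.816.

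**Correlated tests.** The setup was multivariate normal test statistics, 100,000 draws, two-sided 0.05, a common correlation between outcomes and a common correlation between times.

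| Correlation between outcomes | 11 tests, one time |
|---|---|
| 0.3 | 38% |
| 0.5 | 30% |
| 0.7 | 22% |
| 0.9 | 13% |

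| Between outcomes / between times | 33 tests, three times |
|---|---|
| 0.3 / 0.5 | 71% |
| 0.5 / 0.5 | 61% |
| 0.5 / 0.8 | 51% |
| 0.7 / 0.7 | 43% |
| 0.9 / 0.8 | 24% |

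The lowest entry, 13%, is 13 / 5 = 2.6 times the nominal 5%.

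**What control would cost.** With n per arm, the standardized difference detectable with 80% power is d = (z for 1 − α/2 + z for 0.80) × √(2/n). Holm's procedure compares the smallest of eleven p values with 0.05 / 11 = 0.00455, for which z is about 2.838, against 1.960 at α = 0.05.
- 60 vs 60 (strata pooled): (1.960 + 0.842) × √(2/60) = 0.51, rising to (2.838 + 0.842) × √(2/60) = 0.67.
- 30 vs 30 (one stratum): 0.72, rising to 0.95.
- After 20% withdrawal, 48 vs 48: 0.57, rising to 0.75. With 24 vs 24: 0.81, rising to 1.06.

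**The case against.** **The decision rule is not written down.** Section 3.3 does not say that every outcome is tested at every time, or that one significant result suffices. Its analysis of variance could handle time within one model. This stands, so a reader who infers from the text that any of 33 tests may be claimed as efficacy goes beyond it. The single-time figures do not need that inference, although they still need the reading that one positive outcome is enough.

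**A false positive is likely.** A reader might infer this, but it is not established. With 11 tests the chance stays below one half even under independence. With 33 it passes one half only at low to moderate correlation. LH, FSH and their ratio are linked by construction, and repeated measures of one outcome are correlated, so 82% is the independence figure and not the trial's actual rate. Doubling the count to 66 by testing each TCM group separately gives 97%, but that assumes independence and a stratum-by-stratum primary analysis that section 3.3 does not state.

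**Co-primary outcomes do not inflate error.** In the strict sense all must succeed, and then there is no inflation. The article neither uses the term nor states such a rule. These are multiple primary outcomes.

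**It is a pilot, and an analysis plan may exist.** The abstract and section 2.2 do use the pilot label. It would soften the point if no efficacy claim were intended, but section 4.3 intends one. A separate plan could hold an adjustment method, and its absence here is not the finding. The finding is what the article itself fixes: eleven primary outcomes, no main time and a flat threshold.

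**Section 4.2 is only discussion.** It does go on to introduce the three-tier analysis, so it is weak evidence of a rival success criterion. The wording still differs from Table 3 and should be reconciled.

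**Listing oddities in the secondary column.** Age and height appear there as outcomes, and insulin appears on two lines. These do not bear on the primary error rate and form no part of this point.

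**Conclusion.** The point holds in this form: the article names eleven primary outcomes at three times, ranks none of them, and offers one unadjusted 0.05 threshold for a trial expected to validate efficacy. If one significant primary outcome is taken as success, the false-positive chance at a single time is 43% under independence and about 38% to 22% at assumed correlations of 0.3 to 0.7. If all three times are tested it is 82% under independence and about 71% to 24% in the correlated scenarios. Every scenario lies well above 5%, but the exact rate is unknown, because the correlations and the reading rule are assumptions. The documents support saying that the error rate is uncontrolled; they do not support saying that a false positive is more likely than not. The mismatch between section 4.2 and Table 3 is real but secondary.

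**What to change.** Decide before the trial starts. Section 3.4 still puts registration and ethics approval in the future, so the change can precede any data.

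1. Name one primary outcome at one time, for example week 12. Which outcome is the sponsor's choice. Make the other outcomes and times secondary or supportive.
2. If all eleven are to stay primary, apply Holm's procedure across them at one named time.
3. State whether the primary comparison pools the two TCM strata, adjusting for stratum, or is made within each. The strata receive different needling protocols and are sized separately in section 2.2, so this needs an explicit decision.
4. Reconcile section 4.2 with section 3 and Table 3 on the standing of the metabolic profile.

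**Cost.** This is wording in sections 3, 3.3 and 4.2 and in Table 3, and it needs no new measurements if the chosen outcome is one already listed. Fewer outcomes can be called confirmatory. Under Holm, the loss of power shown above has to be accepted or met by re-deriving the sample size at the adjusted level.

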### 2.2. Recruitment, Participants, and Randomization

We propose a two-armed pilot study comparing the effects of active acupuncture (SG) with sham acupuncture (CG). The flow chart of the study design is shown in Figure 2. The sample will be 120 women, divided in two main groups according to the TCM diagnosis: Group A (*n* = 60): kidney deficiency associated with phlegm-dampness syndrome and/or spleen deficiency or liver stasis and group B (*n* = 60): kidney deficiency with main symptoms of blood stasis. Each group should have a total of 60 participants to achieve statistical difference in the case of 20% withdrawal of the participants [34]. Participants will be recruited directly from the family doctor and/or hospital specialty of gynecology/endocrinology. Each medical practitioner will refer patients with PCOS diagnostic aged between 18 and 59 y.o. with main symptoms of metabolic imbalance and women between 18 and 40 y.o. with main symptoms of hyperandrogenism and fertility issues to the principal investigator to be later recruited by telephone interview. Patients who show interest in participating will first be prescreened and recorded by an intake to verify that they meet basic inclusion criteria. All questions about the study, as well as the written informed consent, will be explained in detail. The goal of the screening visit will be to confirm a diagnosis of PCOS and to exclude major medical illnesses. These tests will aim to confirm the western and TCM diagnostic. Women diagnosed with kidney deficiency associated with phlegm-dampness will be randomly allocated by a computer program in a 1:1 ratio to two groups of 30 individuals each, one will be the study group (SGA) submitted to active acupuncture, and the other will be the control group submitted to sham acupuncture (CGA). The same procedure design will be applied to the 60 women diagnosed with kidney deficiency associated with blood stasis (SGB and CGB). All baseline and follow-up measures should be obtained on a single day. However, questionnaires may be spread between the screening and the baseline visit (Table 2).

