### 4.3. What We Expect with the Trial

With the proposed trial, we expect to validate an acupuncture protocol in terms of efficacy and safety that can be a useful tool in the management of symptoms associated with PCOS. With this study design, we expect to find evidence that active acupuncture can be more helpful for promoting follicular development, adjusting the menstrual cycle, and increasing ovulation rate in women with PCOS than sham acupuncture and the long-term effect of the treatment. After active acupuncture treatment, it is expected to find a relative reduction of the biomarkers when comparing to baseline values regarding LH, LH/FSH, total free testosterone, androstenedione, estradiol, BMI, waist circumference, WRH, modified Ferriman–Gallwey score, and Ludwig visual score. We expect an improvement of biochemical hyperandrogenism and HPG axis imbalance, a decrease of androstenedione and sex-hormone-binding globulin, besides the expected decrease in the levels of LH, LH/FSH ratio, total testosterone, estradiol, and on the scoring of the modified Ferriman–Gallwey and Ludwig scales. We expect a possible increase in FSH, progesterone, and the ovulation rate after active acupuncture. With respect to secondary outcomes, we will explore the effect of the acupuncture treatment on metabolic symptoms and expect to describe the metabolic profile of each phenotype before and after the respective treatment. We will adopt international measures as a gold standard for assessing the metabolic status criteria. Besides HOMA-IR improvement, we expect to find a positive correlation between active acupuncture and reduction of the levels of triglycerides, total cholesterol, LDL-C, LDL/HDL, fasting glucose, fasting insulin, and serum insulin and an overview improvement of the metabolic syndrome development. In addition to that, we will try to understand the efficacy of the treatment on exploratory parameters related to the quality of life of the patient, many times disregarded in this type of treatment, especially in anxiety and depression scoring. In this regard, we expect to find a better scoring in the respective questionnaires (reduction in the scoring points of Zung Depression and Anxiety scales and a gain of points in the SF-36 questionnaire) after active acupuncture intervention, particularly in phenotypes where liver fire associated with kidney deficiency originates a lack of mental presence or easy loss of temper. With the results of the study, we also expect to obtain evidence on the possible correlation of phenotypes based on the Rotterdam criteria and those based on the TCM diagnosis proposed by Wang et al., 2017.

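### Section 3.3 fixes no baseline-adjusted between-arm analysis, leaves the randomisation stratum conditional, and gives the planned within-group analysis no stated role

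*Protocol article*

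**What the plan says.** Section 2.2 splits 120 women by TCM diagnosis into groups A and B of 60. Women in group A "will be randomly allocated by a computer program in a 1:1 ratio to two groups of 30 individuals each", and group B is handled the same way, so TCM group is a randomisation stratum. The section allows for 20% withdrawal. Section 3 and Table 2 schedule the outcome measures at baseline, week 6, week 12 and 6 months after the last treatment.

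For the analysis, section 3.3 gives chi-square tests for categorical data and, for continuous data, two-sample t-tests or "Wilcoxon rank sum tests for continuous data, according to whether the data are normally distributed or not". It does not say whether the continuous tests use the final value or the change. Two further sentences matter here: "The variance analysis will be performed for the difference between groups and within the group", and "The stratified analysis will be performed to control the confounding factor if necessary". On women who do not finish treatment it says "we selected intention-to-treat (ITT) analysis to avoid the effects of crossover and drop-out". Among the expected results after active acupuncture, section 4.3 says that "it is expected to find a relative reduction of the biomarkers when comparing to baseline values".

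**The concern.** Three features of the design and analysis do not fit together.

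- **Baseline.** The trial collects a baseline value for its outcomes, but no between-arm analysis that adjusts for it is fixed. Power that costs nothing is left unused.
- **Stratum.** TCM group is built into the randomisation, yet stratified analysis is treated as an optional remedy for an unnamed confounder, with no trigger set in advance.
- **Within-group analysis.** It is planned with no stated inferential role. Women enter because they meet the Rotterdam criteria (section 2.3), so some movement towards normal values in both arms is plausible without any effect of needling. If the active arm's change is significant and the sham arm's is not, that pattern is easily reported as efficacy although it is not a comparison of the arms.

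**Working it through.** **Inputs from the protocol.** Significance at p "value < 0.05 will be considered statistically significant" (two-sided assumed; the text does not say). 30 per arm in each stratum, so 60 per arm pooled. 20% withdrawal gives 60 × 0.8 = 48 per arm pooled and 30 × 0.8 = 24 per arm in one stratum.

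**Inputs assumed, because the protocol gives none.** True difference 0.5 SD of the final value; baseline to follow-up correlation r from 0.4 to 0.7; difference between strata 0 to 1.0 SD; a common change in both arms of 0.2 to 0.5 SD of change.

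**The plan's own figure.** The 60 per TCM group cannot be reproduced: no effect size, SD, event rate or power is stated. Only 48 / 0.8 = 60 can be checked, and the article gives no figure before withdrawal.

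**1. Baseline adjustment.** Relative to an SD of 1 for the final value, the SD is √(2(1 − r)) for a change score and √(1 − r²) after adjustment for baseline. Two-sample t power (noncentral t) with 48 per arm and d = 0.5 divided by that SD:

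| r | Final value | Change score | Baseline-adjusted |
|---|---|---|---|
| 0.4 | 67.9% | 60.0% | 75.3% |
| 0.5 | 67.9% | 67.9% | 79.9% |
| 0.7 | 67.9% | 87.9% | 92.4% |

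Against a final-value test the gain is 7.4, 12.0 and 24.5 points. Against a change-score test it is 15.3, 12.0 and 4.5 points. With 24 per arm in a single stratum, the same formulas give 39.6% for the final value and 45.6%, 49.9% and 66.1% with adjustment.

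**2. Stratum.** With balanced strata whose means differ by D, the unadjusted test uses a variance inflated by about 1 + D²/4, while stratified randomisation keeps that component out of the true error of the arm difference. The effective critical value is therefore about 1.96 × √(1 + D²/4): 2.02 at D = 0.5 and 2.19 at D = 1.0. Two-sided type I error is then about 4.3% and 2.8%. Simulation (20,000 trials, 24 per arm per stratum) gave:

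| D | Type I error, stratum omitted | Power, stratum omitted | Power, stratum included |
|---|---|---|---|
| 0 | 5.0% | 67.6% | 67.7% |
| 0.5 | 4.1% | 66.1% | 68.3% |
| 1.0 | 2.6% | 58.2% | 67.4% |

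The error is on the safe side; the cost is power.

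**3. Within-arm tests.** Let both arms change by the same amount, so that there is no treatment effect. If p is the chance that a paired t-test in one arm is significant in the direction of improvement, the chance that only the active arm is significant is p(1 − p).

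| Common change (SD of change) | 24 per arm | 30 per arm | 48 per arm |
|---|---|---|---|
| 0.2 | 13.0% | 15.0% | 19.9% |
| 0.3 | 20.6% | 22.9% | 24.9% |
| 0.4 | 24.9% | 24.6% | 17.5% |
| 0.5 | 22.7% | 18.6% | 7.0% |

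For example, at 0.4 and 48 per arm, p = 0.775 and 0.775 × 0.225 = 0.174 (0.175 before rounding p). The between-arm test gives a false result in favour of active in 2.5% of trials.

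**The case against.** Much can be said for the plan, and part of it stands.

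- **The tests are valid.** Randomisation justifies unadjusted two-sample tests, and the study is called a pilot. This stands: the loss is of efficiency, and every gain above rests on an assumed effect and correlation.
- **Baseline may be used after all.** The t-test could be on change, and the variance analysis could be a repeated-measures ANOVA that includes baseline. So it would be wrong to say that the plan ignores baseline. What can be said is that no baseline-adjusted comparison of the arms is fixed. A change-score test narrows the gap at r = 0.7 but does worse than final values at r = 0.4.
- **The strata may be analysed separately.** Section 2.2 sizes each TCM group on its own and each has its own point protocol. In such an analysis the stratum term falls away, but the baseline gain remains.
- **The analysts are blinded.** Section 3.1 blinds data analysts and uses an independent statistician. This limits allocation-driven choices about stratification but does not fix the choice.

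Four stronger readings are tempting and are not supported.

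- A reader might infer that incomplete cases are dropped. Section 3.3 states intention-to-treat and excludes no one, and the missing-data method may lie in a document that is not shown.
- A reader might think that omitting the stratum yields false claims. It makes the test conservative.
- A reader might take section 4.3 to define success as change within the active arm. The same section also expects active acupuncture to do better than sham, and it describes expectations, not a success criterion.
- A reader might count every trial in which exactly one arm is significant, which doubles the percentages in step 3. Half of those are sham-only results, which nobody would read as efficacy.

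**Conclusion.** The point holds as a weakness in what section 3.3 fixes; the stated tests are not invalid. It should be corrected before analysis.

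Under a 0.5 SD effect with 48 per arm pooled, prespecified baseline adjustment adds about 7 to 25 points of power over a final-value test, or about 4 to 15 over a change score, for r between 0.4 and 0.7. Omitting TCM group costs nothing if the strata are alike, about 2 points of power if they differ by 0.5 SD and about 9 points if they differ by 1.0 SD.

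The risk of a false efficacy claim comes only from the within-group analysis, and only if its p-values are read as evidence of a treatment effect. The protocol does not say that they will be, but it does not rule it out.

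**What to change.** Reword section 3.3 as follows.

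- **Continuous outcomes.** Make the efficacy test one prespecified between-arm model with the baseline value and TCM group as covariates: either ANCOVA or a repeated-measures mixed model over week 6, week 12 and 6 months. For an analysis run inside a single TCM group, adjust for the baseline value alone.
- **Binary outcomes.** Stratify the arm comparison by TCM group, with Mantel-Haenszel or logistic regression.
- **Stratification sentence.** Remove the condition as far as TCM group is concerned.
- **Within-arm changes.** State that they are descriptive only and that efficacy is judged on the difference between arms.

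The cost is a few sentences and slightly more analysis work. No extra data are needed.
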